## Abstract

**Background:**

Nephrotic syndrome (NS) is characterized by dyslipidemia which is a well-known risk factor for atherogenesis. Atherosclerosis in childhood is mostly subclinical and endothelial dysfunction is known to precede this. Evidence for screening for endothelial dysfunction and cardiovascular risk factors and early identification of premature onset of atherosclerosis in childhood NS remains tenuous in the absence of well-designed prospective studies addressing cardiovascular comorbidity in NS. The objective of our study is to examine endothelial dysfunction and short-term cardiovascular outcomes in a carefully phenotyped cohort of patients with Nephrotic syndrome as compared to healthy controls.

**Methods:**

In a multi-centric prospective cohort study, 70 Steroid Resistant NS (SRNS), 70 Steroid Sensitive (SSNS) patients along with 70 Healthy Controls are being recruited. After a baseline assessment of functional and structural status of heart (2D Echocardiography), arteries (Carotid Doppler and Intima Media Thickness measurements) and microcirculation [a combination of 2D Echocardiography, Laser Doppler Flowmetry (LDF) and Brachial Artery Flow mediated dilation (FMD) and Nail Fold Capillaroscopy (NFC)], the patients are being investigated for endothelial dysfunction. Venous blood sample (15 ml) is being collected for routine investigations and assay of biochemical endothelial markers through Flow Cytometry. The patients will be followed up at 12 months and 24 months after the recruitment to look for any change from baseline period.

**Discussion:**

This study will able to provide a better understanding of the epidemiology of endothelial dysfunction and associated subclinical cardiovascular co-morbidity in childhood NS. Findings on characterization of prevalence of endothelial dysfunction and subclinical markers may be used to design future randomized controlled trials for evaluating the efficacy of preventive and therapeutic interventions in reducing the incidence of cardiovascular disease.

## Background

Nephrotic syndrome (NS) is a common pediatric renal disorder in India. With an estimated prevalence of 12–16 cases per 100,000 population and annual incidence of ~ 1.5–2 new cases per 100,000 population, at least 150,000 to 200,000 cases exist amongst Indian children and about 10,000 new cases are added every year [1, 2]. A child with NS gets exposed to multiple risk factors well known to be atherogenic and contributory to progression of chronic kidney disease (CKD) amongst adults [3, 4].

Apart from hyperlipidemia, a well-known risk factor for coronary artery disease (CAD) and a defining hallmark of NS, these children also get exposed to other risk factors associated with impaired endothelial function and adverse cardiovascular outcomes like high oxidative stress, frequent infections, sustained proteinuria, hypoalbuminemia, thromboembolism, toxicity of steroids and non-steroidal drugs like calcineurin inhibitors (hyperlipidemia,vasculotoxic and nephrotoxic effects). Many children with steroid resistant NS progress towards CKD which is known to increase cardiovascular mortality 500 to 1000 fold compared to the general population in young adults [5]. While hyperlipidemia is usually intermittent and transient in steroid sensitive nephrotic syndrome (SSNS), dyslipidemia and other abnormalities may be persistent in patients with frequent relapses (FRNS) or steroid resistant (SRNS) cases [6].

Biological plausibility of extra-renal endothelial alterations in NS arises from a longstanding recognition of increased glomerular endothelial permeability due to an ill-defined ‘permeability factor’ of extra renal origin. Mediators like platelet activating factor, VEGF family, adhesion molecules of selectin family and Nitric Oxide (NO) pathway are involved in the recruitment of inflammatory interstitial cells as well as affect endothelial cells with widespread vascular effects [1]. Occurrence of hemostatic abnormalities and generalized edema in NS attest to the wide ranging effects related to vascular endothelial dysfunction.

Very few original research studies have addressed endothelial alterations in pediatric NS. Most of the existing published data has related to uncontrolled cross-sectional studies in small number of adults with preponderance of non-minimal change disease. Broadly 3 approaches have been adopted –.

### Vascular function studies

Impaired endothelial responsiveness to specific vasodilator stimuli as a surrogate marker of cardiovascular risk has been studied in both micro-vessels and conduit arteries. Post-occlusive Flow mediated dilatation (FMD) of conduit vessels like radial/brachial artery is a functional assay of nitric oxide bioavailability. Few cross-sectional studies of FMD in NS till date do show a 2–3 fold impairment related to hyperlipidemia but it remains difficult to assess the applicability owing to variations related to small sample sizes, relapse rates and pharmacotherapy. Endothelial function at microcirculatory level has seldom been evaluated in children [7]. Coronary flow reserve, a index of coronary microvascular and endothelial function measured by 2D-Echo, was significantly impaired in adult NS cases versus controls and was related to proteinuria, serum creatinine, total cholesterol and inflammation [8]. Pediatric echocardiographic data for cardiac endothelial dysfunction remains scanty till date.

### Biochemical markers of endothelial dysfunction

Endothelial dysfunction is mediated by NO and all NO synthetases (NOS) are constitutively expressed in the kidney. Serum cGMP, TxA2 and PGI2 have also been found elevated in children with NS [6]. Human serum albumin increases the generation of reactive oxygen species and increases ADMA generation by endothelial cells in a dose-and-time-dependent manner in rat models of NS [6]. While studies have addressed NO pathways in relation to steroid responsiveness, no study has primarily looked at NO pathways in relation to endothelial dysfunction in children with NS. CD146 is a novel cell adhesion molecule localized at the endothelial junction that increased in physiopathological settings linked to endothelial junctional alteration [9–11]. sCD146 circulates in the plasma of healthy subjects. Modifications of its basal levels could reflect alterations of junctional functions such as vascular permeability. In the only study of CD146 in relation to other markers of endothelial cell injury in patients with NS, amongst 45 CAPD patients, 43 patients with nephrotic syndrome and 25 healthy volunteers, amongst various markers of endothelial cell injury, all markers except selectins were significantly elevated in patients with NS and CAPD when compared to the healthy volunteers.

### Circulating angiogenic cells as markers of endothelial dysfunction

Assessment of circulating endothelial cells (CECs), endothelial progenitor cells (EPCs) and their derivatives like microparticles and sCD146 would form a novel approach towards defining endothelial dysfunction in childhood NS. In FSGS, levels of CECs were noted to be higher during active stage [12]. In asymptomatic adults with definite exposure to cardiovascular risk factors, levels of circulating EPCs were a better predictor of vascular reactivity than conventional risk factors [13].

Akin to the dearth of data on endothelial dysfunction in childhood NS, subclinical cardiovascular comorbidity of childhood NS also remains poorly characterized. Ambulatory BP monitoring reveals a high prevalence of systolic hypertension in association with increased carotid intima media thickness (cIMT) and endothelial dysfunction [14]. Symptomatic as well as asymptomatic cardiac thrombi have been described in case reports in both SSNS and SRNS. In cross sectional studies, 50% of children with NS showed left ventricular hypertrophy which correlated with carotid stiffness and systolic hypertension while increased Left Ventricular Mass index was detectable in 19% cases [8, 14]. A positive correlation of increased cIMT with number of relapses has been observed in 3 out of 4 published cross sectional studies in childhood NS [13, 14]. Effect of relapse frequency was notable as early as 1 year of disease duration and persisted even after completion of steroid therapy 4 years to 15 years ago and was related to lipid levels. Multiple abnormal subclinical CVD markers were present in 16% and independently associated only with higher LDL cholesterol.

Experimental and clinical studies suggest that increased cholesterol levels, hypoalbuminemia and reduced oncotic pressure induce endothelial cell dysfunction. Akin to CAD, diabetes and hypertension, there is a higher incidence of NS amongst South Asians [1, 15]. This ethnic predisposition towards adverse outcomes, high burden of NS in our population, lack of reliable long term risk estimates for adverse cardiovascular outcomes in children with chronic renal conditions coupled with observations of insulin resistant dyslipidemic state which persists beyond remission, definitely merit further investigation of potential atherogenicity and cardiovascular comorbidity associated with childhood NS amongst Indians.

The primary objective of this study is to define extent of endothelial dysfunction by noninvasive evaluation for impairment of macrovascular and microvascular endothelial function in children with NS versus healthy controls, by assessment of brachial artery Flow mediated dilation (FMD) and cutaneous post-occlusive reactive hyperemia (PORH), respectively. Secondary objectives includes (a) To prospectively evaluate the temporal course of progression of endothelial dysfunction over 24 months of follow-up of these children in the macrovascular and microvascular endothelium as defined by repeating brachial artery FMD and cutaneous PORH (b) To evaluate in these children the association between endothelial dysfunction and morphological markers of subclinical cardiovascular comorbidity, defined by measurement of carotid intima media thickness (cIMT) and abnormalities on Nail Fold Capillaroscopy (NFC) and echocardiography (c) To look for numerical abnormality of circulating angiogenic cells and micro-particles as a marker of endothelial dysfunction in children with NS versus healthy controls, and (d) To assess biochemical marker of endothelial dysfunction in children with NS versus healthy controls.

### Ethical considerations

Study Protocol has been approved from Local Institutional Ethics Committee of AHRR and AIIMS participating centre.

### Design of study

Prospective cohort study.

## Inclusion and exclusion criteria

### Phase i: Case recruitment & baseline assessment of biomarkers of endothelial dysfunction

#### Cohort a: Children with Nephrotic syndrome (NS)

Consecutive cases of NS fulfilling the following criteria will be enrolled from the Pediatric Nephrology OPD of the participating institutions.

##### Inclusion

a) Age 1 and < 18 years age b) Estimated GFR > 60 ml/min/1.73 m2 c) Willingness to follow-up for subsequent 24 months.

##### Exclusion

a) Family history of premature atherosclerosis/stroke or familial hyperlipidemia b) Acute kidney dysfunction/injury at the time of recruitment c) Statin therapy at the time of recruitment d) Active systemic vasculitis e) Coexisting primary cardiovascular anomalies f) Anomalies of the limbs preventing diagnostic procedures g) Children with serious bacterial infection or thromboembolic episode will be recruited only after 12 weeks from the acute episode.

#### Cohort B: Healthy controls

Healthy siblings of the recruited children with NS between 1 and 18 years age. Children will be deemed healthy only if normotensive, with eGFR > 60 ml/min/1.73 m2 and with no systemic illness or serious bacterial illness in the preceding 12 weeks.A detailed phenotyping of the disease profile and exposure to cardiovascular risk factors will be done for each child using a combination of clinical and laboratory examination. In addition a detailed nutritional assessment including dietary recall will be done in each child. Routine case specific laboratory assessments for clinical management of an individual case will continue as per standard treatment guidelines of Indian Society of Pediatric Nephrology [16, 17].Baseline assessment of functional aberrations in microvascular and macrovascular endothelium will be done using LDF for cutaneous PORH and B-mode ultrasound for brachial artery FMD respectively.Baseline screening for cardiovascular comorbidity will be done using 2D-echocardiography, high-resolution ultrasonography of carotid arteries and NFC.In case of child being in relapse at the time of recruitment, a repeat assessment will occur at 12 weeks after the baseline assessment. Comparison of FMD and PORH between relapse and remission in same child will assess any short term effect of disease activity on these parameters.

### Phase ii: Prospective follow up and cardiovascular outcomes assessment

Children will be followed up to monitor the clinical course and undergo management of Nephrotic syndrome as per existing standard consensus guidelines [16, 17].Noninvasive assessment of biomarkers of endothelial dysfunction and subclinical cardiovascular comorbidities along with biochemical estimates of cardiovascular risk will be carried out at defined time points.At the end of 24 months from recruitment for a given case, final reclassification of disease phenotype based on the temporal profile of relapses/remission and steroid sensitivity will be done to categorize the subjects into the following categories as per standard definitions of Indian Society of Pediatric Nephrology [16, 17]: a. Steroid sensitive nephrotic syndrome (SSNS) b. Steroid resistant nephrotic syndrome (SRNS) c. Healthy controlsVenous blood plasma (in tubes containing EDTA (1.8 mg/ml) and citrated vials after centrifugation at 1500 rpm for 30 min at 4 degree Centigrade) and urine samples will be collected at baseline, 12 and 24 months and stored at − 80 C for batch assay of biochemical markers of endothelial dysfunction at a later date.

### Consent and recruitment

Witnessed written informed consent will be requested from all eligible patients or their next of kin (in case of patients with lower age group). Literate subjects or their next of kin will be requested to give their written consent by one of the physician investigators with a research staff witnessing the consent. Subjects or their next of kin who are not literate will have the contents of the consent form read out and explained by the investigator and their left thumb impression will be taken according to the current practice with a nurse as a witness. All questions from the subjects or their next of kin will be answered by the investigator. Potentially eligible patients will be recruited from the outpatient department and ward of the participating centre. Written informed assent will be obtained for children > 12 years age apart from oral assent for all children > 7 years of age in the presence of parents/legally authorised representatives.

### Baseline assessment

Standardized case record forms will be used to record patient history, general and NS examination. Clinical, laboratory and radiological findings are to be recorded.

### Protocols for noninvasive assessments

#### General protocols

All investigations will be carried out in a minimum 4 h fasting state with parents instructed to refrain from giving any caffeinated drinks or chocolates in preceding 24 h as per standard guidelines [18–21]. Child will be acclimatized to a quiet room with comfortable temperature (22–25 °C) for at least 20 min prior to the testing in presence of the parents with informed consent. Timing of testing will be same time of the day for each child.The individual carrying out the investigation will be blinded to the clinical status of the child.At the time of study only image/data acquisition will occur. All images and electronic raw data will be captured, anonymized and stored in an electronic imaging repository established for this purpose for an offline analysis in a blinded manner. Image analysis and laboratory investigations will occur in a blinded manner by an investigator blinded to the clinical status of the child.For each investigation methodology, quality controls will be maintained by noting the inter-observer and intra-observer variability. It will be periodically assessed by rescanning of a random sample of 10 children with NS and 10 healthy controls. Coefficients of variability, intra-class correlation coefficients, and Bland Altman plots will be used for assessing variability.All invasive blood sampling will follow the noninvasive testing.

#### Specific protocols

A.Endothelial Dysfunction [18–21]
I.Microvascular Endothelial Function Equipment and method

Laser Doppler Flowmetry (Moor LDI 2 SIM; Moor Instruments Ltd., Axminster, UK) for quantification of post-occlusive reactive hyperaemia (PORH) which refers to the increase in skin blood flow following a brief arterial occlusion.

##### Technique

Brachial artery will be occluded using a pressure cuff placed around the upper arm and inflated up to 250 mmHg above the systolic blood pressure for 5 min followed by a quick deflation. Blood perfusion will be measured in Perfusion Units (PU) using a patented stepwise movement of the laser beam across the tissue to minimize background noise with a penetration depth of around 1 mm.

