##### Equipment and method

High-resolution ultrasonography with 2D, color, and spectral Doppler imaging with high-frequency linear-array transducer (7 to 12 MHz) and ECG gating and digital recording, an automatically deflating pneumatic blood pressure cuff and stereotactic probe-holding device. Determination of FMD of the brachial artery following release of a 250 mmHg cuff occlusion for 5 min. The post-occlusive hyperemia leads to a shear stress over endothelium and consequent nitric oxide release and dilatation.

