### Strategies to minimize losses to follow-up

All the patients will be followed up at 12 and 24 months after the baseline assessments. To minimize the risk of retrieval bias, two to five telephone numbers (both mobile and landline) along with their army service number will be noted from the patients or his/her relatives at the time of recruitment. A trained research worker will attempt to contact the participants one month, one week and two days prior to their respective follow up.

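### The cuff pressure for the PORH test is worded so that, read literally, it allows systolic pressure plus 250 mmHg in children; it is probably a slip for an absolute 250 mmHg and should be corrected

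*Protocol article*

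**What the plan says.** The Technique paragraph under Microvascular Endothelial Function describes the PORH test. A cuff on the upper arm occludes the brachial artery and is "inflated up to 250 mmHg above the systolic blood pressure for 5 min followed by a quick deflation". The neighbouring paragraphs on equipment and endpoint, and the general protocols for noninvasive assessments, add no absolute pressure and no upper limit for this test.

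FMD is described separately under Macrovascular Endothelial Function. Its method statement reads "Determination of FMD of the brachial artery following release of a 250 mmHg cuff occlusion for 5 min", and its own Technique paragraph repeats the plain 250 mmHg, with the cuff below the antecubital fossa.

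The children tested are those meeting the age criterion "Age 1 and < 18 years age" and the controls, defined as "Healthy siblings of the recruited children with NS between 1 and 18 years age". PORH is one of the two measures named in the primary objective. It is also repeated: the first secondary objective follows progression over 24 months "as defined by repeating brachial artery FMD and cutaneous PORH". The follow-up section says "All the patients will be followed up at 12 and 24 months after the baseline assessments". For a child in relapse at recruitment, "a repeat assessment will occur at 12 weeks after the baseline assessment".

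**The concern.** The sentence expresses the cuff pressure relative to systolic pressure but attaches a number that makes sense as an absolute pressure. Its plain grammatical meaning is systolic plus 250 mmHg. That is more than is needed to stop arterial flow, because a pressure above systolic is enough and 250 mmHg on its own is well above any systolic value assumed here.

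The stake is tolerability. The instruction applies to young children, some of them healthy siblings, for five minutes at a time and at more than one visit. A secondary stake is clarity. The words 'up to' set a ceiling and not a target, so the sentence fixes no single occlusion pressure on either reading. Two institutions take part, and both need an instruction with one meaning.

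**Working it through.** **Inputs**

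- PORH pressure as written: up to systolic + 250 mmHg for 5 min (Microvascular Endothelial Function, Technique).
- FMD pressure: 250 mmHg absolute for 5 min (Macrovascular Endothelial Function, Equipment and method, and Technique).
- Age of the children: from 1 year to under 18 (Inclusion).
- Systolic pressure: not given in the article. The range 80 to 130 mmHg is an assumption of this review.

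**Formulas**, with S the child's systolic pressure

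- Literal ceiling = S + 250.
- Excess over an absolute 250 mmHg = (S + 250) − 250 = S.
- Margin above systolic at an absolute 250 mmHg = 250 − S.

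| Quantity (mmHg) | S = 80 | S = 130 |
|---|---|---|
| Literal ceiling | 80 + 250 = 330 | 130 + 250 = 380 |
| Excess over absolute 250 | 330 − 250 = 80 | 380 − 250 = 130 |
| Margin above systolic at absolute 250 | 250 − 80 = 170 | 250 − 130 = 120 |

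The excess is always the child's own systolic pressure. An absolute 250 mmHg stays above systolic throughout the assumed range, so the extra pressure is not needed to exceed systolic.

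The upper figure of 380 mmHg depends on the assumed range. Controls must be normotensive, but the exclusion list for children with nephrotic syndrome does not mention hypertension. A child with a systolic pressure above 130 mmHg would have a literal ceiling above 380 mmHg.

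**Which reading is likely.** The FMD paragraphs give the same figure, 250 mmHg, and the same duration, 5 min, as an absolute pressure. The PORH phrase may be a compressed way of saying 250 mmHg, that is, above systolic. This makes a slip probable. It does not prove one, because FMD is a different test with a different cuff position and its setting does not govern PORH.

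**The case against.** The strongest reply is that this is a copy-editing matter. If the phrase is a slip, no child receives 330 to 380 mmHg and the tolerability issue never arises in practice. 'Up to' does not oblige an operator to reach the ceiling, and the stated purpose, occlusion of the artery, is met at any pressure above systolic. The article is also a condensed account that ties its vascular methods to cited standards, so operators may be working from a fuller procedure. Finally, the article gives no threshold for harm against which to judge the excess.

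Much of this stands, and it is why the point is minor. It does not remove the point. The article chose to state the pressure, and stated it in a form whose plain meaning is too high. The intended value can be inferred but not confirmed from the text. A procedure applied to children should not depend on the operator guessing that the sentence is wrong.

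A reader might infer four stronger conclusions, which the article does not support:

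- *That children are being harmed.* No harm threshold is given, and nothing shows that any inflation exceeded 250 mmHg.
- *That the PORH and FMD settings contradict each other.* They are separate tests with the cuff at different sites, so different pressures would not in themselves be inconsistent.
- *That results are biased or power is lost.* On either reading the cuff is meant to occlude the artery, and nothing in the article links the wording to a difference between groups or to the sample size.
- *That every scheduled PORH test in the planned 70 + 70 + 70 children can be counted as affected.* The sample size section reaches 70 per group only at the end of 36 months, and a child enrolled after month 12 cannot have a 24-month visit by then. The follow-up calculation requires only 50 children with nephrotic syndrome and 50 controls. Besides, a count of scheduled tests is not a count of tests at excess pressure, which on the probable reading is zero.

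**Conclusion.** The concern holds as a minor fault of wording in an operative instruction for one of the two primary measures. As written, the PORH cuff pressure may go to about 330 to 380 mmHg, assuming systolic pressures of 80 to 130 mmHg. This is 80 to 130 mmHg more than an absolute 250 mmHg, and no other part of the article limits it. Confidence is high that the wording is faulty. That 250 mmHg absolute was intended is probable but unconfirmed. The consequence is limited to tolerability and to the lack of one clear procedural target.

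**What to change.** Ask the investigators to confirm the intended pressure. Then rewrite the sentence in the PORH Technique paragraph as one absolute pressure that is both the target and the maximum, for example: inflated to 250 mmHg (suprasystolic) for 5 min. Send the correction to both centres so that operators use the same setting.

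The cost is a one-line correction and a short note to two sites. Sample size, endpoints and analysis are unaffected.
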